#### Exclusion criteria

2.3.2

Suffered high energy injury or multiple injuries, with multiple fractures in other parts of the body.Ipsilateral lower extremity once broken seriously or experienced major surgery.Patients with malignant tumors.Patients with pathological fractures.Patients refused to receive hemiarthroplasty.

### Randomization and allocation concealment

2.4

The random number will be generated by SAS Institute Inc., Cary, NC, USA, and then put into an opaque envelope, with the attention to concealment of randomization. Participants can be randomly assigned to either group. The participants will receive an opaque envelope given by independent researchers and allocated to one of the 2 groups according to the serial number and group name printed on their treatment card.

### Blinding

2.5

In this study, patients in the monitoring group need to wear a special motion monitoring devices and interact with doctors online; the implementation of the blind method is difficult, so the form of open clinical research is adopted. However, in the functional test of patients (Harris score of hip joint, life ability assessment, etc.), the evaluators were blinded, and a third person independent of the experiment was invited for data sorting and analysis. The study code will not be revealed until the end of the study unless there is a serious adverse event (AE).

### Interventions

2.6

The participants in both groups will be given the same basic 3-state rehabilitation treatment. Combined with current literature research and clinical experience, the exercise program was developed by 10 senior orthopedic trauma specialists and 1 rehabilitation therapies, which is activity training involves 3 major joints (hip, knee, and ankle), early weight-bearing, gait training and strength training of lower limb muscles. The detailed program will be provided in Figure 2. This exercise prescription is only for the early recovery after HA. On this basis, the amount of exercise can be added as appropriate according to their situation and the doctors advice after 2 weeks. All the subjects received the same routine treatment of prevention of infection, anticoagulation, and pain relief after HA; however, they should not accept a series of exercise programs arranged by other rehabilitation professionals.

**Figure 2 F2:**
[figure not shown]
Exercise program.

#### The control group

2.6.1

The patients of this group of the control group will carry out the staged rehabilitation exercises according to the definite exercise plans, and record the daily exercise in Figure 3 and give it to the doctors during the follow-up. The doctor in charge needs to repeatedly preach and teach during hospitalization to ensure that patients and their families understand the importance of postoperative rehabilitation exercise, and give family exercise guidance after 2 weeks (the same as the experimental group). Regular outpatient follow-up after discharge. If patients have any questions about the rehabilitation process, they should call for a consultation, and do not take the initiative to call for follow-up. Two weeks, 1 month, 3 months, and 6 months after the operation, an outpatient face-to-face examination will be carried out.

**Figure 3 F3:**
[figure not shown]
Daily practice record.

#### The monitoring group

2.6.2

The following interventions were implemented based on the control group: patients should additional use intelligent rehabilitation assistant system (including lower limb motion monitoring devices and interconnect display terminals). The system can collect patients movement times, the amplitude of movement, lower limb weight, and so on, and upload feedback information on the WeChat official account. If patients doubt the rehabilitation process, they could ask the chief physician online questions through the official account. The official account of WeChat will send a reminder of rehabilitation and exercise every day and give the family exercise guidance after 2 weeks (the same as the control group). Two weeks, 1 month, 3 months, and 6 months after the operation, an outpatient face-to-face examination will be carried out.

The intelligent rehabilitation assistant system involved in this study produced by YILIFE Information Technology Ltd Co, which consists of 2 parts: motion detection equipment and WeChat official account (an interactive platform). The motion detection equipment needs to be worn in different parts of lower limbs, it can observation and exactly record the number of joint movements, range of motion, lower limb muscle strength and walking ability (stride, walking distance), shown in Figure 4 and Figure 5. According to the clinical experience and pre-experimental data, a stander is set up. Only when the practice meets the stander, it could be considered as a successful exercise and recorded as a successful exercise by the machine. For example, you are a patient in stage 1, your ankle extension for 1 second, failed to reach the specified 3 seconds, the monitor will record your motion pattern, but it will not be recorded as a successful exercise. As for the WeChat official account, WeChat is a social software widely used in China, which can be mastered by the elderly. Participants whether in each group would follow the WeChat official account under the guidance of researchers, and researchers will release a video tutorial on rehabilitation exercises. Participants in the control group should record their daily exercise, as for the monitoring group participants, they could get practice feedback from monitor records and be reminded of the task they have completed or not.

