#### The secondary outcome

2.7.2

The Secondary outcome measures are as follows:

Activity of Daily Living (ADL): it refers to the necessary activities that a person carries out every day to meet the needs of daily life, including eating, dressing, washing, bathing, toileting, dressing, etc. Functional movement includes turning over, sitting up from bed, transferring, walking, driving a wheelchair, going up and downstairs, etc. The total score is 100 (100 points: life self-care; 60 points and above: basic self-care; 40 to 60 points: life needs assistance; 20 to 40 points: life needs great assistance; less than 20 points: life completely dependence.)The timed “up & go” text: a fast and quantitative evaluation method of functional walking ability only needs a chair and a stopwatch. During the assessment, the patient is sitting on the chair with the back of the chair and hands on the armrest. If the walking aid is helpful, the walking aid is held in the hand. The reference object set 3 meters away from the seat. With the tester sends out the command of “start”, the patient stands up and walks to the reference point and returns. There is none physical help during the test. The tester records the time taken (in seconds) and the risk of falling during the completion of the test. Before the formal test, the patient is allowed to practice 1 to 2 times to ensure that the patient understands the whole test process. Researchers need to record the complete time of the experiment and evaluate the risk of completing the action. (1 point: normal. 2 points: very slight abnormality. 3 points: slight abnormality. 4 points: moderate abnormality. 5 points: severe abnormality.)Visual analog scale (VAS): The subjects participating in the study will indicate the intensity of their pain using a VAS of 100 mm. They must signal on a horizontal line of 100 mm where they would place their pain, where 0 mm indicated “no pain” and 100 mm would be “the worst pain imaginable”.Postoperative complications: Such as pulmonary embolism, lower extremity deep vein thrombosis, loosening, and displacement of the prosthesis, periprosthetic fracture, postoperative infection, etc.6-month mortality after HA:

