### Data management and statistical analysis

2.10

Data are collected from electronic medical records at the study sites, participants study-specific diaries. All collected data for the trial is entered electronically in the encrypted database built by the researchers ourselves which could not be accessed by a third party. The system sets a fixed personal account according to the users organization and role. All attempts to log in to the system will be recorded. All data changes are recorded by user and time, so it can be tracked. All the research data were collected in the First Affiliated Hospital of Guangzhou University of Traditional Chinese Medicine, part of which was recorded in the orthopedic ward and some in the outpatient department. The data management system will check whether all the input data are of correct type, for example, the date must be valid date, and the number must be valid number, at the same time, logical check/verification is designed. Composition of data monitoring committee (DMC) will be undertaken by the Ethics Committee of the First Affiliated Hospital of Guangzhou University of Traditional Chinese Medicine and responsible for reviewing data security once a year.

The statistical analysis will be carried out by IBMSPSS Statistics 21 software. Demographic and baseline data will be summarised using descriptive statistics and graphs as appropriate. Continuous variables will be summarised by descriptive statistics. Categorical variables will be summarised in frequency tables. For the contrast of intragroup hypotheses, Student *t-*test for paired variables will be applied in the case of parametric distribution and Kruskal–Wallis H for nonparametric distributions. Kolmogorov Smirnov test will be used to test the normality of variables. One-factor analysis of variance (ANOVA) will be used in the case of parametric distributions and Kruskal–Wallis H for non-parametric distributions. Statistical tests used to compare between treatments groups will be done two-sided at a signifi-cance level of 5%. The confidence level used will be 95% (0.05), and the power of the study will be 90% (0.1).

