### Criteria for stopping treatment

2.11

Participants could stop the treatment and drop out of the research project for any reason at any time, and the reason for the drop out will be recorded in their CRF. The participants will be told that they have the right to drop out of the experiment and that they will be provided the standardized treatment if they drop out. The criteria for stopping treatment and dropping out from the research project are:

The participant has suffered from a serious medical disease, and could not receive surgical treatment or rehabilitation exercise according to the plan.The participant could not have a regular follow-up or cooperate with telephone follow-up.Poor compliance, such as unable to have a regular follow-up or cooperate with telephone follow-up.In addition to the standardized treatment of the Department, a whole set of exercise plans of other rehabilitation physicians were implemented.

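### Complications may be recorded unequally between arms, because contact between visits differs and evaluator blinding is stated only for functional tests

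*Protocol article*

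**What the plan says.** Section 2.7.2 of the protocol article lists the outcome with examples and an open end: "Postoperative complications: Such as pulmonary embolism, lower extremity deep vein thrombosis, loosening, and displacement of the prosthesis, periprosthetic fracture, postoperative infection, etc". Section 2.10 adds that "Statistical tests used to compare between treatments groups will be done two-sided", at the 5% level.

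On contact outside the visits, the two arms are described differently:
- Monitoring group (2.6.2): when patients are in doubt about their rehabilitation, "they could ask the chief physician online questions through the official account". The account also sends a daily exercise reminder, and the device returns feedback on the exercises.
- Control group (2.6.1): patients with questions about rehabilitation are told that "they should call for a consultation, and do not take the initiative to call for follow-up".

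Both arms attend the same outpatient examinations at 2 weeks and at 1, 3 and 6 months. The text closing section 2.7.2 says the outcome variables are measured at weeks 2, 4, 12 and 24 by a trained evaluator.

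On data sources, section 2.10 says: "Data are collected from electronic medical records at the study sites, participants study-specific diaries". Section 2.5 describes the trial as open and states evaluator blinding for functional tests, naming the Harris score and the assessment of life ability. Complications are not named there.

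Section 2.11 gives as one ground for stopping: "The participant could not have a regular follow-up or cooperate with telephone follow-up". It names no arm.

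**The concern.** A comparison of complication counts is fair only if events are looked for equally hard in both arms. Here one arm has an easier route to a senior clinician between visits. A swollen leg or an inflamed wound noticed during exercise is a natural reason to use it. If the contact leads to an entry in the medical record, the event can reach the data even if it has resolved by the next visit. The same event in a control who does not telephone may not be recorded. The open-ended list of complications leaves some judgement about what counts, and the article does not say that whoever makes that judgement is unaware of the arm.

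At stake is the safety reading of the device. Fuller recording in the monitoring arm would make the device look less safe than it is, or hide a real reduction in complications.

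**Working it through.** **Step 1. The arms side by side**

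| Feature | Monitoring | Control | Section |
|---|---|---|---|
| Face-to-face visits | 2 weeks; 1, 3, 6 months | the same | 2.6.1, 2.6.2 |
| Outcome measurement | weeks 2, 4, 12, 24 | the same | end of 2.7.2 |
| Route for questions | online to the chief physician | patient telephones | 2.6.1, 2.6.2 |
| Prompts | daily exercise reminder, device feedback | no reminder described; not actively called | 2.6.1, 2.6.2 |
| Follows the WeChat account | yes | yes | 2.6.2 |

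The scheduled part is equal and the unscheduled part is not. The later gaps between visits are 12 − 4 = 8 weeks and 24 − 12 = 12 weeks, long enough for a mild event to come and go. Since section 2.10 also draws on medical records, the visits are not stated to be the only way an event is counted.

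**Step 2. Possible size**

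The article has no complication rate to reproduce. The one input taken from it is 25 patients per arm (section 2.9). The rest is assumed: the same true risk in both arms, 10% to 30%; detection of 90% to 95% in the monitoring arm and 70% to 80% in the control arm.

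Recorded rate = true risk × detection share.

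| True risk | Monitoring | Control | Difference | Patients of 25 | Risk ratio |
|---|---|---|---|---|---|
| 10% | 0.10 × 0.90 = 9.0% | 0.10 × 0.80 = 8.0% | 1.0 point | 0.25 | 0.90/0.80 = 1.13 |
| 20% | 0.20 × 0.95 = 19.0% | 0.20 × 0.70 = 14.0% | 5.0 points | 1.25 | 0.95/0.70 = 1.36 |
| 30% | 0.30 × 0.95 = 28.5% | 0.30 × 0.70 = 21.0% | 7.5 points | 1.88 | 0.95/0.70 = 1.36 |

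One patient in 25 is 4 percentage points. If the visits pick up every event in both arms, the difference is zero.

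**Step 3. Would it produce a false positive test?**

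Fisher's exact test is used here as an illustration: two-sided, 25 per arm, full detection in the monitoring arm, equal true risk.

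| True risk | Control detection 100% | 80% | 60% |
|---|---|---|---|
| 20% | 2.2% | 3.0% | 6.0% |
| 30% | 2.3% | 3.7% | 9.4% |

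The entries are the chance of p ≤ 0.05. The largest relative gap assumed in step 2, 0.70/0.95 = 0.74, lies between the 80% and 60% columns. The chance passes 5% only in the 60% column. The problem is therefore a distorted estimate more than a false significant result.

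**Step 4. Masking**

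Suppose the device truly lowers risk from 20% to 12%, a risk ratio of 0.12/0.20 = 0.60. With full detection in the monitoring arm and 80% in controls, the recorded ratio is 0.12/(0.20 × 0.80) = 0.75. With 60% in controls it is 0.12/(0.20 × 0.60) = 1.00.

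**The case against.** A reader might infer that complications will be detected more fully in the device arm. The article does not support that, for these reasons:
- All patients have the same four examinations, and the outcomes are measured there by a trained evaluator.
- The daily contact is an exercise reminder. No enquiry about symptoms is described.
- The online route is for doubts about rehabilitation, and controls can telephone with the same questions. The difference is one of ease of access.
- Monitoring care is built on control care, so the absence of active calls may apply to both arms.
- The prescribed intervention lasts 2 weeks. The article does not say whether the online route stays open afterwards.
- Nothing says that online questions are entered in the medical record.
- If the telephone follow-up in section 2.11 operates in both arms, the asymmetry shrinks.

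These points stand, and they reduce the claim from will to may. Severe events (pulmonary embolism, displacement, periprosthetic fracture) should surface in either arm, and 6-month mortality is not affected.

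It can also be said that a condensed article leaves event definitions and forms to the full protocol or case report form. That is fair, and the absence of a checklist is not the point made here. The point is what the article does state: unequal contact, a second data source beside the visits, and blinding whose stated scope does not include this outcome. Identical visits do not remove the risk unless the comparison rests on what those visits elicit.

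**Conclusion.** The concern holds in a limited form. Mild or silent complications arising between visits may be recorded unequally, and the article states no blinding for their assessment. The direction of the recorded difference is not fixed either, because the extra contact is part of the intervention and may itself lower the true risk.

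The size cannot be derived from the documents. The 1 to 7.5 points, or at most about 2 patients in an arm of 25, rests wholly on the assumed risks and detection shares. The Harris score, activities of daily living, timed walking test and pain scale are scheduled assessments and are not affected by this route.

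Separately, sections 2.6.1 and 2.11 do not fit together: one appears to rule out calls to controls, while the other makes failure to cooperate with telephone follow-up a ground for stopping. That needs no assumption. Overall this is a minor point on a secondary outcome.

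**What to change.** In section 2.7.2, state that complications are elicited in both arms with the same fixed checklist at the four existing visits and classified by an evaluator blinded to arm. For every event, record how it came to notice: visit, telephone, online or hospital record. Keep all events in the safety report, and add a sensitivity comparison restricted to visit-elicited events. Excluding online-only events from the comparison altogether would be worse: it would drop genuine complications, and it would not close the route while hospital records still count.

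Reconcile sections 2.6.1 and 2.11 on telephone follow-up, and state whether it applies to both arms.

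The cost is a short form at visits already planned and one extra tabulation, with no added visit. It should be in place before enrolment, since control-arm events that nobody asked about cannot be reliably recovered later.

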**Figure 4 F4:**
[figure not shown]
Rehabilitation monitor. Note: a. Physical picture of monitoring equipment, b&c. Exercise with the monitor.

**Figure 5 F5:**
[figure not shown]
Motion waveform recorded in Wechat background.

### Outcome measurement

2.7

#### The primary outcome

2.7.1

The primary outcome is a change in the Harris Hip Score (HHS). HHS is used most commonly as a postoperative functional evaluation tool for hip fractures. The following 7 symptoms can be evaluated by HHS: the degree of the pain, the daily activity function, gait, walking aids, walking distance, deformity degree, and activity scope. The score is judged and recorded by researchers with a totally 100 (excellent: 90∼100, fine: 80∼89, secondary: 70∼79, and not satisfactory: <70), the higher scores indicating better joint function.

#### The secondary outcome

2.7.2

The Secondary outcome measures are as follows:

Activity of Daily Living (ADL): it refers to the necessary activities that a person carries out every day to meet the needs of daily life, including eating, dressing, washing, bathing, toileting, dressing, etc. Functional movement includes turning over, sitting up from bed, transferring, walking, driving a wheelchair, going up and downstairs, etc. The total score is 100 (100 points: life self-care; 60 points and above: basic self-care; 40 to 60 points: life needs assistance; 20 to 40 points: life needs great assistance; less than 20 points: life completely dependence.)The timed “up & go” text: a fast and quantitative evaluation method of functional walking ability only needs a chair and a stopwatch. During the assessment, the patient is sitting on the chair with the back of the chair and hands on the armrest. If the walking aid is helpful, the walking aid is held in the hand. The reference object set 3 meters away from the seat. With the tester sends out the command of “start”, the patient stands up and walks to the reference point and returns. There is none physical help during the test. The tester records the time taken (in seconds) and the risk of falling during the completion of the test. Before the formal test, the patient is allowed to practice 1 to 2 times to ensure that the patient understands the whole test process. Researchers need to record the complete time of the experiment and evaluate the risk of completing the action. (1 point: normal. 2 points: very slight abnormality. 3 points: slight abnormality. 4 points: moderate abnormality. 5 points: severe abnormality.)Visual analog scale (VAS): The subjects participating in the study will indicate the intensity of their pain using a VAS of 100 mm. They must signal on a horizontal line of 100 mm where they would place their pain, where 0 mm indicated “no pain” and 100 mm would be “the worst pain imaginable”.Postoperative complications: Such as pulmonary embolism, lower extremity deep vein thrombosis, loosening, and displacement of the prosthesis, periprosthetic fracture, postoperative infection, etc.6-month mortality after HA:

These variables will be measured in the pre-evaluation, first evaluation (week 2), second evaluation (week 4, short-term), third evaluation (week 12, medium-term), and fourth evaluation (week 24, the end of the study). These evaluations will be carried out by an evaluator trained in these procedures, and the data will be stored in an Excel document.

Baseline information of diagnosis and treatment, such as gender, age, comorbidities, imaging, previous self-care ability, injury mode, fracture classification, and potential previous treatment, such as other site fractures, soft tissue injuries, osteoporosis, etc, will be collected from participants medical records.

### Participants timeline

2.8

A brief Standard Protocol Items: Rehabilitation and evaluation schedule is provided in Table 1.

**Table 1 T1:** Rehabilitation and evaluation schedule.

	Study Period							
	Enrolment	Allocation	Post-allocation (treatment)			Follow-up (evaluation)		
Timepoint	0 week	HA	1 day	1 week	2 weeks	4 weeks	12 weeks	24 weeks
Enrolment:								
Eligibility screen	×							
Informed consent	×							
Clinical Evaluation and Inclusion-Exclusion Criteria	×							
Allocation		×						
Interventions:								
Manual Therapy Protocol			×	×	×			
Therapeutic Exercise Protocol			×	×	×			
Sham Protocol			×	×	×			
Assessments:								
Demographic Data	×							
Neck Disability Index					×	×	×	×
Visual Analog Scale					×	×	×	×
Pressure Pain Threshold					×	×	×	×
Overall Balance Index					×	×	×	×

